## 2 Background Information

### 2.1 Name and description of the investigational product(s).

Tricomponent acellular pertussis vaccine: contains 25ug pertussis toxoid, 25ug filamentous haemagglutinin, 8ug pertactin, 0.5mg aluminium salt.

### 2.2 A summary of findings from nonclinical studies that potentially have clinical significance and from clinical trials that are relevant to the trial.

#### 2.2.1 Disease burden from early infant pertussis:

In the past decade, there has been a resurgence of pertussis in Australia and other developed countries with long-established immunisation programs, in those over the age of 10 years (waning immunity) and infants under the age of 5 months (too young for full immunization). Unimmunised infants are most likely to develop severe disease requiring hospitalization, frequently complicated by apnoea, seizures, encephalopathy or death. Available data on pertussis in Australia include notifications to public health, hospitalizations and deaths. Pertussis notification rates in infants aged less than 6 months remain higher than any other age group, despite maximal pertussis vaccine coverage in older children. Infant hospitalisations average 400 per year, more than 80% before 5 months of age. (Figure 1) Five months is the earliest the two doses needed for significant protection can be reliably delivered under current immunisation schedules. Approximately 35% of hospital admissions occur before 8 weeks of age (Figure 1) Of the 18 deaths coded as due to pertussis in Australia 1993-2004, all but two were less than 6 months of age. Death certificate records are thought to underestimate infant deaths from pertussis by a factor of at least 3.

**Figure 1: Pertussis hospitalisations under 12 months of age 1994-2004 (n=4114) **

[figure not shown]

Worldwide, some 300 000 children under 5 years old die each year from pertussis. This same pattern of pertussis affecting infants who are too young to have received vaccination is also seen in other countries with high levels of immunisation, such as Germany and the UK. In countries such as Australia with high immunisation coverage in children adults, particularly parents, are the most important source of infection for infants,

#### *2.2.2 Current childhood pertussis vaccine coverage and immunisation schedules:*

Pertussis immunisation schedules differ significantly around the world but currently do not start earlier than 6 weeks of age. The World Health Organisation (WHO) recommends a schedule 6, 10, 14 weeks for primary immunisation against pertussis and a 2,3,4 month schedule is used in many European countries. Australia follows the US schedule of primary immunisation at 2, 4 and 6 months. The Australian Childhood Immunisation register (ACIR) records that by the age of 12 months, 92% of children have received 3 doses, but successive doses are more likely to be delayed, especially in Indigenous infants. Accelerated schedules reduce delay in subsequent doses. The first dose of pertussis-containing vaccine is licensed for use from 6 weeks of age and is accepted as a valid dose by the ACIR when given at 6 weeks.

#### *2.2.3 Potential strategies for prevention of early infant pertussis:*

Strategies to reduce early infant pertussis have been summarised and are discussed below.

##### Maternal immunisation during pregnancy:

Maternal vaccination has been extremely successful in preventing neonatal tetanus in developing communities, but for pertussis has significant hurdles. First, licensure of any therapeutic substance in pregnancy is difficult and even when recommended often has low uptake, such as seen with maternal influenza vaccination. Second, although there is some suggestion that passively transferred maternal antibody provides some protection, this is not universal and declines rapidly after birth. Third, maternal levels wane rapidly, so re-vaccination may be necessary. Studies of maternal Pa vaccination are in progress, supported by the National Institutes of Health in the US and by industry sponsors in Canada.

##### Cocooning of infants through parental immunization:

Parents are the single most common identified source of pertussis transmission to infants, though a source is often not known. In Australia, USA, France, Austria and Germany it is recommended that all persons who come into contact with newborns receive a dTpa booster shortly after delivery – a “cocoon” strategy. High vaccination coverage is difficult to achieve unless funding and distribution is directly supported, which is not currently the case in Australia or elsewhere.

##### Direct protection of infants through newborn immunisation:

The desirability of vaccination at the youngest possible age was recognised in the 1940s because of high mortality among neonates. Successful neonatal vaccination must result in the early protective immunity, be well tolerated and safe. Only BCG and Hepatitis B vaccines are routinely administered at birth.

### **2.3 Summary of the known and potential risks and benefits, if any, to human subjects.**

#### **a. Whole cell pertussis vaccines**

Vaccination against pertussis at birth with whole cell pertussis (Pw) was studied from the 1940s, but questions about immune tolerance discouraged later studies Although the study which raised concerns that Pw vaccine in the first week of life might be followed by immune tolerance was small and poorly designed it was influential in discouraging further pursuit

of early vaccine schedules. However, Galaska and Halsey's review in 1984 concluded that the overall evidence for tolerance was weak. Early studies of Pw vaccines measured only agglutinins, had small numbers of subjects and often did not give data on responses prior to dose 3. A more recent study, comparing a 2,3,4 month DTPw schedule with 3,5,9 months, found that while D and T antibody titres were lower for the accelerated schedule, PT was non-significantly higher. The conclusion that tolerance following early DTPw was not a major problem was also supported by a US study. Unlike Pw, the response to acellular pertussis (Pa) vaccine seems less likely to be interfered with by maternal antibody; Pa has replaced Pw in most rich countries .

#### Acellular pertussis vaccines

As trials to measure disease endpoints in neonates are unfeasibly large, all studies of Pa-containing vaccines given at birth must rely on antibody responses as surrogate markers of protection. Three small studies have recently been completed in Italy Germany, and the USA. The studies differ in several ways, including the vaccine and schedule used (Table 1). Our pilot study (CHW ethics approval 2003/07) conducted from 2005 to 2007 included an arm with 2 Pa doses before 8 weeks. This demonstrated significantly higher antibody by 8 weeks in the 2-dose group. (Manuscript attached)

**Table 1: Studies of Pa vaccine at birth**

|                                       | Italy | USA | Germany | Australia |
|---------------------------------------|---------------------------|-------------------------|-----------------------------|-------------------------------|
| Sample size                    | n= 91                     | n= 50                   | n=110                       | n=76                          |
| Birth vaccine used             | DTPa                      | DTPa                    | Pa                          | Pa                            |
| Manufacturer                   | Chiron                    | Sanofi Aventis          | GSK                         | GSK                           |
| Schedule                       | 3, 5, 11 months           | 2, 4, 6 months          | 2, 4, 6 months              | 1, 2, 4, 6 months             |
| Antibody post dose 2 (2 to 3m) | PT only                   | Not measured            | PT, PRN, sig higher         | PT, PRN, sig higher           |
| Reduced antibody @ 7 months    | yes                       | yes                     | no                          | no                            |

The pilot study results, in the context of disease burden timing above, have established that 2 doses prior to 8 weeks is likely to be beneficial and set the scene for a more definitive study examining a readily implementable accelerated schedule to achieve this.

## **2.4 Description of and justification for the route of administration, dosage, dosage regimen and treatment period(s).**

### *Rationale For Study Design And Key Questions From Our Pilot Study:*

#### *2.4.1 Concomitant antigen responses:*

Other vaccine antigens co-administered with Pa-containing vaccines include diphtheria, tetanus, polio, Hepatitis B and *Haemophilus influenzae* type b (Hib). In the German study, attainment of Hib antibody responses indicating protection (>0.15ug/ml) was significantly lower after the first 3 doses (88% vs. 98%). Reduced Hib immunogenicity has been associated with DTPa-Hib combination vaccines, but has only emerged as a clinical problem in the UK prior to that country introducing a Hib booster. In Australia, a Hib booster has always been routine.

There was no significant difference in response to other antigens. In our pilot study, hepatitis B antibody levels were non-significantly lower in the birth Pa group, but all participants were above the accepted threshold for protection (>10mIU/L). This study will examine IgG responses to D, T, Hib and hepatitis B post primary immunisation.

#### *2.4.2 Influence of maternal antibody:*

The effect of pre-existing maternal pertussis Abs, particularly higher levels resulting from maternal immunization, on responses to Pa vaccines at birth or subsequently is uncertain. Our pilot data suggest that two doses of Pa vaccine (at birth and 1-2 months old) are immunogenic in the presence of detectable maternal antibody, but did not include immunised mothers. Since 2007, NSW Health has required that all healthcare workers with patient contact be given dTpa booster vaccination and non-mandatory guidelines are in place in other jurisdictions. As healthcare workers participate more commonly in vaccine trials, this should facilitate recruitment to a study arm with mothers immunised with dTpa. Irrespective of the results of maternal immunisation studies, the question of persistence of adequate antibody in subsequent pregnancies remains.

#### *2.4.3 Timing and interval of Pa vaccine:*

Our study suggests that two doses of Pa vaccine, the first as soon as possible after birth and the second separated by a minimum of 4 weeks, give optimal PT IgG levels. Observational studies suggest some level of protection even from one dose. In Germany, protective efficacy against infant hospitalisation was 68% after the first and >90 % after the second dose of DTPa. In Sweden, the incidence of pertussis fell from 230-235 (cases per 100 000 person years) after zero or one dose of pertussis vaccine to 52 after two doses. Pilot data from both the Australian and German birth Pa vaccine trials showed significant rises in antibody after the second dose, at 4 and 8 weeks of age respectively. A second dose at 6 weeks of age should be similar, but is more feasible and practical, as current combination vaccines including Pa are licensed from this age and considered a valid dose by the ACIR from 6 weeks. A second dose at 6 weeks of age aligns with routine well baby checks, reducing delivery costs, and is consistent with the current WHO schedule.

#### *2.4.4 Cellular immune responses:*

Our pilot study showed that infants who received Pa vaccine at birth had a significant increase in IL5 and IL13 cytokine (TH2) responses to pertussis vaccine antigens at 7 months compared to those vaccinated later. There were no differences in IFN $\gamma$  and cytokine (TH1) responses to other vaccine antigens between groups. This suggests that birth Pa vaccine results in a TH2 bias, restricted to pertussis responses, compared to controls and raises the question of altered responses following subsequent natural pertussis exposure. Detailed profiling of infant T-cell immunity in response to neonatal pertussis vaccination is thus an essential component of this study.

#### *2.4.5 Validity of surrogate measures of protection against pertussis from vaccination:*

Evidence to support the validity of surrogate immunologic measures comes from animal studies and vaccine trials. These trials were conducted in countries with a high incidence of disease (Italy, Germany, Sweden) not using the Pw vaccines then available. The composition of currently available Pa vaccines was determined by detailed immunogenicity studies under the auspices of the US National Institutes of Health. Despite the limited evidence for association between specific levels of individual antibodies and protection against disease, there has been a pragmatic need to measure antibody markers of immune response to Pa vaccines. In the National Institutes of Health (NIH) sponsored comparative immunogenicity trials for acellular pertussis vaccines, seroconversion to PT and PRN measured by ELISA

was defined as a 4x increase in pre-immunisation Elisa Unit (EU) value, to at least 4x the minimum detectable level. The minimum detectable levels were 2 EU for PT and PRN.

All acellular vaccines include **pertussis toxin (PT)** as it is only present in *Bordetella pertussis*, and appears to be the most important single factor in protection against severe disease. All current commercially available vaccines also contain **pertactin (PRN)**, an attachment factor protective in the mouse respiratory challenge model. Human data on the correlation between antibody and protection come from household contact studies including vaccine trial participants, allowing pertussis following known exposure to be correlated with post-vaccination antibody. The Swedish study found a statistically significant efficacy of 75% (95% CI 0-96%) against typical pertussis when measurable antibody levels to both PT and PRN were present post primary vaccination. The German study found protection significantly correlated only with PRN. Despite limitations in the evidence for specific antibody thresholds and protection against disease, these measures are deemed sufficient for global licensure by all regulatory bodies and the overwhelming body of evidence suggests antibody to both PT and PRN has a role in protection. Accordingly, we have adopted a dichotomous classification, with measurable IgG to both PT and PRN deemed to indicate at least short-term protection against severe disease.

## **2.5 A statement that the trial will be conducted in compliance with the protocol, GCP as defined by the International Conference on Harmonisation and the applicable Australian regulatory requirement(s).**

This trial will be conducted in compliance with the protocol, GCP as defined by the International Conference on Harmonisation and the applicable Australian regulatory requirements.

## **2.6 Description of the population to be studied.**

Healthy newborns, greater than 36 completed weeks gestation, will be randomized to receive acellular pertussis vaccine and hepatitis B vaccine at birth (within 120 hours of birth) or hepatitis B vaccine alone.

# **3 Trial Objectives and Purpose**

## **3.1 Detailed description of the objectives and the purpose of the trial.**

Currently, vaccines to protect against pertussis (whooping cough) are given from 2 months of age, but almost one third of infant hospitalisations for pertussis occur prior to 2 months. Some early studies of older pertussis vaccines suggested that vaccination at birth was not appropriate. However, these studies were small and their results are no longer relevant in the acellular pertussis vaccine era. Three small recently published studies of acellular pertussis vaccine at birth suggest that this has advantages.

This study aims to randomly assign a group of newborn infants to birth acellular pertussis (Pa) vaccine versus current standard practice. Infants will either receive a Pa-containing vaccine at birth and then 6 weeks, four and six months of age or the standard schedule with the first dose given at 6 rather than 8 weeks. Antibody responses in the blood, which are believed to correlate with protection, will be compared at 6 weeks, 10 weeks, 6 months and 8 months of age. This study aims to show whether earlier vaccination gives better protection from pertussis at the time when babies are most likely to die from this infection.

## 3.2 HYPOTHESES

1. IgG antibody responses to pertussis toxin (PT) and pertactin (PRN) in infants receiving monovalent acellular pertussis vaccine (Pa) at birth and routine vaccines at 6 weeks are significantly higher than in unvaccinated infants by 10 weeks of age, and remain higher at 6 and 8 months of age
2. Cell-mediated immune responses to PT and PRN at 10 weeks and 8 months of age in infants receiving monovalent acellular pertussis vaccine at birth and routine vaccines at 6 weeks do not differ significantly from those in infants with first doses at 6 weeks.
3. IgG antibody responses to **PT and PRN** at each time point in infants of mothers vaccinated with dTpa within the previous 5 years do not differ significantly from infants of unvaccinated mothers.
4. In infants receiving Pa at birth and routine vaccines at 6 weeks, the prevalence of antibody levels consistent with protection to **other vaccine antigens** is not significantly reduced
5. The frequency, duration and intensity of solicited symptoms in the 6 days following vaccination and unsolicited symptoms until the next vaccination visit (up to 8 months old) will not differ significantly between the infants receiving Pa vaccine at birth and controls.

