## 11 Assessment of Efficacy

### 11.1 Specification of the efficacy parameters.

Blood samples will be taken as follows: maternal blood at birth, infant blood at 6 weeks, 10 weeks, 6 and 8 months. We believe that each of these blood samplings is important in the evaluation of antibody kinetics and comparison of the two groups in terms of presumed disease protection.

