### 14.2 The number of subjects planned to be enrolled.

#### 14.2.1 Antibody measures:

Lack of any measurable antibody to both PT and PRN is the best available indicator of susceptibility to severe pertussis. Accordingly, we have based sample size calculations on reduction in the proportion of susceptible infants as early as possible. If superiority of birth pertussis vaccine is defined as a reduction of 12% or more in the proportion of subjects

lacking antibody (no measurable PRN or PT) compared with controls at 10 weeks old, a sample size of 220 in each maternal arm will have 80% power to detect a reduction of this magnitude at a two-sided alpha level of 0.05. This is not altered by a differing prevalence of detectable pre-immunisation antibody among controls over the range of 65% to 75%. (Sample Power V2 [www.spss.com](http://www.spss.com)) This study will recruit 110 participants in each of the 4 arms, a total of 440 participants allowing for a 10% drop out rate.

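### Hypothesis 3 treats infant IgG at 6 and 10 weeks as a response, although it contains passively acquired maternal IgG, so the early comparison by maternal dTpa status cannot show whether the infant's response is altered

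*Protocol*

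**What the plan says.** Hypothesis 3 (Protocol section 3.2) concerns IgG responses to PT and PRN and states that these "at each time point in infants of mothers vaccinated with dTpa within the previous 5 years do not differ significantly" from those in infants of unvaccinated mothers. Section 3.1 lists the time points: antibody responses "will be compared at 6 weeks, 10 weeks, 6 months and 8 months of age". The first secondary objective (section 4.2) asks whether maternal dTpa in the past 5 years influences infant antibody or cellular responses.

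The samples are "maternal blood at birth, infant blood at 6 weeks, 10 weeks, 6 and 8 months" (section 11.1). No cord or infant birth sample is listed. Under section 5.3 and Table 2 the control group has its first pertussis-containing dose at 6 weeks, and the 6-week blood is listed before that dose.

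Section 14.1 analyses log-transformed serum concentration in a linear model with group, site and maternal dTpa status as factors. Nothing in the protocol separates maternal from infant IgG.

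The background recognises maternal antibody. Section 2.2.3 says there is some suggestion that "passively transferred maternal antibody provides some protection, this is not universal and declines rapidly after birth". Section 2.4.2 says that the effect of maternal pertussis antibody, "particularly higher levels resulting from maternal immunization, on responses to Pa vaccines at birth or subsequently is uncertain". Section 14.2.1 allows for a "differing prevalence of detectable pre-immunisation antibody among controls over the range of 65% to 75" per cent. Section 2.4.5 cites a definition of seroconversion relative to the pre-immunisation value, but hypothesis 3 does not use it.

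**The concern.** Hypothesis 3 names a response, but what is measured is total IgG. In controls at 6 weeks there has been no vaccine to respond to, so a difference between maternal strata at that visit reflects antibody acquired from the mother. In the birth group at 6 weeks, and in both groups at 10 weeks, the measured value is a sum of two parts. Maternal vaccination is expected to raise the maternal part. Whether it lowers the infant's own part is the question the objective asks.

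The two effects have opposite signs, so the comparison can go wrong in two ways. Real suppression can be partly or wholly cancelled, and because the prediction is non-significance with no margin, cancellation would look like confirmation. Alternatively, passive antibody alone can produce a difference that is read as an altered response. Either error would mislead on how infants of immunised mothers respond to a birth dose.

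**Working it through.** **The plan's own figure.** Hypothesis 3 has no sample size of its own. The only antibody figure is 220 per randomised group (section 14.2.1). A pooled two-sided chi-square test at 5% with 80% power for a 12-point reduction needs 224 per group if 35% of controls lack antibody, or 198 if 30% do (198/0.9 = 220). The figure reproduces, and the present point does not depend on it.

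**Step 1: controls at 6 weeks.** Section 5.3 and Table 2 place the first control dose at visit 2, after the blood sample. This IgG therefore cannot be a vaccine response. No numerical assumption is needed.

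**Step 2: algebra at 10 weeks.** Let A be the infant's own IgG without suppression, b the fraction suppressed, and M_u and M_v the residual maternal IgG for unvaccinated and vaccinated mothers.
- Totals: A + M_u against A(1 − b) + M_v.
- Exact cancellation occurs when b = (M_v − M_u)/A.

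**Step 3: illustration.** The protocol gives no titres or half-life, so these are assumptions: half-life 30 to 45 days; 6-week maternal IgG of 5 EU with an unvaccinated mother and 5k EU with a vaccinated one; own response to the 6-week dose of 15 EU, halved to 7.5 EU by suppression. Visit 3 is 28 to 35 days after visit 2 (section 8.3.2).
- Residual fraction r = 2^(−d/half-life). At d = 28: 0.52, 0.58 and 0.65 for half-lives of 30, 36 and 45 days. At d = 35: 0.45, 0.51 and 0.58.
- Ratio of totals = (5kr + 7.5)/(5r + 15).

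| Maternal gap k | Ratio with 50% suppression, over both days and all half-lives |
|---|---|
| 4 (5 v 20 EU) | 0.95 to 1.12 |
| 3 (5 v 15 EU) | 0.82 to 0.95 |
| 2 (5 v 10 EU) | 0.69 to 0.77 |

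Without maternal antibody the ratio would be 0.50. With no suppression at all it is (5kr + 15)/(5r + 15). For k = 4 this is 1.39 (r = 0.445) to 1.53 (r = 0.65), a difference due to passive antibody alone.

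**Step 4: a second set of assumptions.** Take A = 20 EU, half-life 28 to 50 days, and passive IgG at birth of 5 to 20 EU with unvaccinated mothers and 2 to 3 times that with vaccinated ones. At about day 73 the passive excess exactly cancels a suppression of 4% to 73%. For example, with half-life 36 days, 20 EU and a ratio of 2, M_u = 20 × 2^(−73/36) = 4.90 and M_v = 9.81, so b = 4.91/20 = 25%.

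The simulation used a true 30% suppression, 99 v 99 infants (110 per cell less 10%), ln SD 0.8 for own and 0.9 for passive IgG, and birth levels of 10 to 20 EU. A was held at 20 EU at every visit.

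| Sample | Runs with a significant difference | GMC ratio |
|---|---|---|
| Own component alone | about 87% | 0.70 (true) |
| Raw IgG, about day 73 | 4% to 90% | 0.84 to 1.34 |
| Raw IgG, about day 190 | 15% to 85% | 0.71 to 0.91 |
| Raw IgG, about day 257 | 57% to 87% | 0.71 to 0.80 |

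In the central case (36 days, 20 EU, ratio 2) the day-73 ratio is 0.997, significant in 4% of runs. In the 90% case the ratio is 1.34, so the significant result points the wrong way.

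**Step 5: later visits.** With half-lives of 30 to 45 days, the share of 6-week maternal IgG left at the earliest 6-month sample (day 176, 134 days later) is 4.5% to 12.7%. At the earliest 8-month sample (day 236, 194 days later) it is 1.1% to 5.0%. The 8-month sample is the cleaner of the two.

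**The case against.** Total IgG is a deliberate choice. Section 2.4.5 takes measurable IgG to PT and PRN as a marker of short-term protection, and for that purpose its source does not matter. Section 3.1 also uses the word response loosely for levels at all four visits. This stands: raw early IgG is a valid measure of presumed protection. The fault lies in using it to judge whether maternal dTpa alters the infant's response.

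A reader might infer that suppression will be hidden and reported as no effect. The protocol does not support that. Near-complete masking in Step 3 needs about a fourfold maternal gap, and a gap of that size would itself appear at 6 weeks. Among 99 controls per stratum, ln 4 = 1.39 is 0.92 SD even with an ln SD of 1.5, and power exceeds 99.9%. Hypothesis 3 would then be contradicted at 6 weeks, although by passive antibody and not by a response. The gap may also be small: section 2.2.3 says "maternal levels wane rapidly, so re-vaccination may be necessary", and section 5.2 admits dTpa up to 5 years earlier. Suppression that persists could still be seen at 6 and 8 months.

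An SAP may exist that adjusts for maternal titre or the 6-week value, and section 14.1 leaves covariate models open. That could help at 10 weeks. It would not make 6-week IgG in controls a response.

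A reader might also infer that the primary result is compromised. It is not. The week-10 comparison is between randomised groups within maternal strata, so passive antibody is balanced in expectation.

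**Conclusion.** The point holds as a defect in how hypothesis 3 is framed. For controls at 6 weeks it follows from the schedule alone. For the birth group at 6 weeks and both groups at 10 weeks, the outcome mixes two effects of opposite sign, so it can partly mask suppression or present passive transfer as an altered response.

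How far this goes is not known. In the Step 3 illustration a 50% suppression ranges from invisible to plainly visible as the assumed maternal gap falls from fourfold to twofold. These figures rest on assumed titres, half-lives and SDs, and they show possibility, not expected failure. The 6- and 8-month comparisons are much less affected, the 8-month one least. Secondary objective 1 is affected; the primary objective's randomised antibody comparison is not. The change should be made.

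**What to change.** Restate hypothesis 3 as follows:
- The claim about maternal dTpa and the infant's antibody response rests on raw IgG at 8 months (main) and 6 months.
- IgG at 6 weeks in controls is reported by maternal stratum as passively acquired antibody.
- IgG at 6 weeks in the birth group and at 10 weeks in both groups is reported by maternal stratum as total antibody (presumed protection), and not as evidence for or against a blunted response.

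Any correction of 10-week IgG for the expected maternal residual should be exploratory, with its assumptions stated. Subtraction can give zero or negative values that cannot be logged. In the birth group it would rely on an average transfer ratio. Section 5.2 also allows for mothers vaccinated after delivery but before enrolment, whose visit-1 blood may not reflect what was transferred.

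The cost is rewording and relabelled tables, with no new samples. The downside is that the maternal-effect question is answered later, at 6 and 8 months, and the early samples no longer support a response claim.
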